## Assignment of interventions: Blinding

### Who will be blinded {17a}

Apart from ICRF research staff who will administer either the IMP or placebo, all trial participants, care providers, outcomes assessors, and data analysts will be blinded to the study arm allocation of each participant for the duration of Stage 1 of the trial.

ICRF research staff will be blinded to outcomes collection and analysis.

The Independent Data Monitoring Committee (IDMC) and study statistician preparing the IDMC report will require access to fully unblinded data.

### Procedure for unblinding if needed {17b}

#### Emergency unblinding

The trial EDC system will include an automated unblinding facility, in case unblinding is required. In the event that emergency unblinding of an individual participant is required, authorised staff (as documented on the delegation log) will follow trial procedures to unblind the participant in question and proceed with expedited reporting if required.

Investigators are encouraged to discuss the need for emergency unblinding with the Sponsor / CI (or designee) if the circumstances permit such a discussion. If discussion prior to emergency unblinding cannot take place, the coordination centre should be informed afterwards.

#### Unblinding following viral rebound

Participants in both study arms will be unblinded once viral rebound has been confirmed.

Participants will attend the research clinic, and the local study team will unblind the participant, discuss the arm the patient had been assigned to, and explain next steps, i.e. arm A to restart ART immediately and continue study visits, and arm B to restart ART + bNAb if they wish to continue with the study.

Unblinding will occur using the automated facility within the Openclinica system.

#### Unblinding for statistical analysis

When performing safety and interim analyses, the integrity of trial blind should be maintained, with the exception of the IDMC who will have access to fully unblinded data. The Study Statistician preparing the IDMC report will also require access to fully unblinded data in order to prepare the report. Unblinding in these cases should take place in accordance with Imperial Clinical Trials Unit (ICTU) Standard Operating Procedures (SOP) and documented accordingly.

### Data collection and management

### Plans for assessment and collection of outcomes {18a}

#### Screening tests

The following blood tests will be performed at screening to confirm eligibility, tests will be analysed via local laboratories:
HBV surface antigen or HBV PCRHCV PCR or core antigenHTLV-1Serologic tests for syphilis: rapid plasma reagin (RPR)Liver function tests (LFTs): serum ALT, bilirubin, aspartate transaminase (AST), albumin, alkaline phosphatase (ALP)Biochemistry: serum sodium, potassium, phosphate, calcium, urea, creatinine, glucose, lipids, and cholesterol levelsHaematology: haemoglobulin, white cell count and differential, platelets, clotting (INR), prothrombin time, activated partial thromboplastin time and fibrinogen, CD4 count, CD8 count, CD4:CD8 ratioHIV VLBlood samples will be collected at screening to measure SARS-Cov-2 antibody level.

A urine sample will also be taken at screening to assess the following:
Urine protein creatinine ratio (uPCR)For female participants, a urine dipstick pregnancy test will be performed

A swab sample will also be collected at screening to determine the eligibility and will be assessed via local laboratories:
PCR to detect SARS-Cov-2

#### Screening bNAb sensitivity:

In order to be eligible for recruitment to RIO, candidates need to assessed to be sensitive to both bNAbs. To assess sensitivity, viral sequences in blood samples from candidates will be screened prior to their recruitment to the trial.

Proviral HIV DNA is extracted from peripheral blood mononuclear cells (~ 20 × 10^6^) and HIV Env genes from single proviruses are amplified using the single genome amplification assay, which is based on limiting dilution nested polymerase chain reaction. A minimum of 20 Env genes per candidate will need to be successfully sequenced using Illumina technology to confer a final result. A computational algorithm will be used to determine the sensitivity of all sequences from each candidate, by checking specific residue positions on the protein chain [22].

Participants with viral sequences that appear to be resistant to one or both bNAbs will not be eligible to participate in RIO.

#### Blood tests after screening:

The following blood tests will be repeated as indicated; tests will be analysed via local laboratories:
LFTs (*weeks 1, 2, 4, 8, fortnightly till viral rebound*)Biochemistry: (*Stage 1: screening visit, dosing visit, week1, viral rebound visit and 12 weeks post-viral rebound. Stage 2 visits include: week 1, week 2, and 12 weeks after viral rebound*)*Full blood count (FBC) as per visit schedule*, CD4 count, CD8 count, CD4:CD8 ratio, and HIV VL (*all visits*)

#### Urine test after screening

At IMP/placebo dosing and weeks 1, 4, and 8, a urine dipstick test will be performed to check protein and blood.

For female participants, the pregnancy test will be repeated prior to dosing with IMP/placebo and again at the end of the study.

#### SARS-CoV-2 symptom checks and PCR test

Coronavirus symptoms screening will be performed at all visits. Swab samples (SARS-Cov-2 PCR) will be taken at screening and repeated only if symptoms of COVID-19 disease are reported throughout the trial follow-up.

Participants positive for SARS-Cov-2 at screening visit will be re-screened (swab sample for SARS-Cov-2 PCR), once fully recovered from COVID-19 illness and wish to join or re-join the study protocol.

#### Viral load and CD4 count monitoring

This is described under interventions and in Fig. 2.

#### Exploratory / research samples:

Additional blood samples will be taken from consenting participants over the course of the trial for research purposes to help understand the mechanisms underpinning the trial outcomes. While the plasma load is undetectable, every 2 weeks, additional research samples (four 9 ml acid-citrate-dextrose (ACD) tubes) of blood will be taken for research analyses.

Analysis of research samples will be carried out at the research laboratories at the University of Oxford in the UK and Rockefeller University in the USA.

The details of the bleeds and volumes are given in the schedules in Tables 2 and 3. The main assays to be undertaken are detailed in Table 4.

**Table 4 Tab4:** Summary of key research assays

Assay	Sample	Purpose	Time-point
T cell immunology			• Pre-ART where available • On ART • Pre-bNAb • Fortnightly during ATI • Following viral suppression
HIV-specific T cell intracellular cytokine staining for CD4 and CD8 phenotypic and functional responses	PBMC	Screen CD4 and CD8 T cell responses to HIV in response to bNAbs	
HIV ELISpots: γ-interferon responses with peptides targeted according to ICS responses	PBMC	Higher resolution analyses of specific responses to peptide level and how they are impacted by intervention	
CD8 tetramer responses targeted to specific peptides	PBMC	Further in-depth resolution of CD8 T cell functionality at cellular level	
HLA Class I and II typing (4-digit)	PBMC	Profiling of HLA alleles to shape immune responses and confer advantage/disadvantages	
T cell killing assays	PBMC	Functional killing assay to augment intracellular cytokine staining data	
Natural Killer (NK) cell responses			
Flow cytometry for NK cell phenotype and function	PBMC	Characterisation of NK function and profile in response to bNAbs	
ADCC and NK cell killing	PBMC	Functional assessment of bNAbs using characterised killing protocols	
NK-like population analyses (flow cytometry)	PBMC	High resolution characterisation of cells that fall between the innate and adaptive responses	
Virology			
Next-generation sequencing (NGS) single genome amplification (SGA) of HIV ENV: bNAb sensitivity	PBMC	Env sequencing to screen for bNAb sensitivity	Screening
Full length HIV sequencing	Plasma CD4 T cells	Full length haplotype analysis of viral and proviral populations pre and post intervention to determine correlations with response	• Pre-ART (virus) where available (HEATHER cohort) • On ART, and pre-ATI (provirus) • Rebound (virus) • Post resuppression (provirus)
HIV Integration site analysis	CD4 T cells	Understanding of clonality of viral reservoir and relationship of integration sites to reactivation potential and susceptibility to inhibition	Pre-ATI
HIV DNA and cell-associated RNA quantitation	CD4 T cells	Standard molecular analyses of proviral and HIV transcript quantitation, both surrogate markers of persistent infection and biomarkers of remission and rebound	• Pre-ART where available (HEATHER cohort) • On ART • Pre-bNAb • Pre-ATI • Post resuppression
Host genomics			
Transcriptome profiling* *Initially bulk, but with single-cell 10× resolution dependent on results	CD4 and CD8 T cells NK cells	Full host genomic analyses at bulk and single cell (likely tetramer driven for CD8 cells) to understand host determinants of outcomes	• Pre-ART where available (HEATHER cohort) • On ART • Pre- ATI
Pharmacokinetics and anti-drug antibodies			
bNAb pharmacokinetics Quantitation of ‘anti-drug antibodies’ (ADA)	Plasma	To determine bNAb plasma concentrations To determine development of inhibitory antibodies against bNAbs	• Post bNAb infusion

#### Peripheral blood mononuclear cells (PBMC) and plasma samples

Blood samples (between 50 and 200 ml depending on the time-point) for the collection of PBMCs and plasma will be taken to evaluate the parameters detailed in Table 4.

For arm A, samples will be collected according to the schedules in Table 2 at the following time-points: screening, dosing visit, week 8, 24, and 36 after ATI, at viral rebound on restarting ART, following resuppression 16 weeks after ART restart. For participants who maintain undetectable VL off ART after 36 weeks, a 50-ml blood sample will be taken fortnightly until rebound or the end of the study.

For arm B, samples will be collected according to the schedules in Table 3 at the following time-points: screening, dosing visit, weeks 8, 24, and 36 after ATI, at viral rebound on restarting ART. For participants who maintain undetectable VL off ART after 36 weeks, a 50-ml blood sample will be taken fortnightly until rebound or the end of the study.

Then, bloods will be taken again at bNAb dosing (1 week after ART restart), at start of 2nd ATI 24 weeks later, 8 weeks after start of 2nd ATI, and then fortnightly from 24 weeks after the 2nd ATI until rebound or the end of the study. Following rebound and ART restart, bloods will be taken at restart and following resuppression 16 weeks after ART restart.

#### Quality of life (HIV PROM)

A participant-reported outcome measure (PROM) will be completed at baseline, 2 weeks after commencing the ATI and then at the end of the study to evaluate quality of life of participants. The PROM to be used has been developed by Harding et al. [14], is patient-centred, and enables multi-dimensional measurement of health-related quality of life for people with HIV.

### Plans to promote participant retention and complete follow-up {18b}

Participants will be reimbursed for their time and travel costs, £120 for the randomisation visit (lasting up to a full day), and £25 for all other visits.

#### Discontinuation of study treatment or study withdrawal

Participants may discontinue study treatment for the following reasons:At the request of the participantAdverse event / serious adverse eventAllergic reaction to the investigational medicinal productWithdrawal from the study (defined as discontinuation of study treatment and study procedures) for the following reasons:Participant decisionLoss to follow-upProcedures for withdrawal from the studyIf a participant permanently discontinues the trial intervention, they will be invited to continue to attend trial visits if possible, to allow for collection of key outcomes and safety data.If a participant withdraws from trial procedures, an assessment must be made as to whether trial data and samples collected to date can be retained and analysed for the trial. If the participant does not agree for data and samples collected to be retained, the samples must be destroyed, and data excluded from the analyses.Participants who have discontinued the trial intervention and/or have withdrawn from the trial will not be replaced, as the sample size for Stage 1 allows for potential loss to follow-up.Data management {19}

#### Source data

Source documents include original documents related to the trial, to medical treatment and to the history of the participant, and adequate source documentation must be maintained at participating sites to allow reliable verification and validation of the trial data. What constitutes source data for this trial will be outlined in the trial monitoring plan (Supplement file 1).

#### Language

CRFs will be in English. Generic names for concomitant medications should be recorded in the CRF wherever possible. All written material to be used by participants must use vocabulary that is clearly understood and be in the language appropriate for the study site.

#### Database

Trial data will be collected on an electronic case report form (eCRF). Data is entered into the EDC system by trained site personnel. All data recorded in the eCRF will be signed off by the Investigator or his/her appropriate designee. All changes made following initial submission of data will have an electronic audit trail with a date. Specific instructions and further details will be outlined in the study-specific eCRF manual.

#### Data collection

The principal means of data collection from participant visits will be Electronic Data Capture (EDC) via the internet using the Openclinica database. Data will include demographics, vital signs (blood pressure, heart rate, temperature, weight and height at screening only), physical examination (including COVID-19 symptom checks), blood test results, and questionnaire data.

Details of procedures for eCRF completion will be provided in a study-specific manual.

#### Documentation and data storage

The investigator must retain essential documents until notified by the Sponsor, and for at least 10 years after study completion. Participant files and other source data (including copies of protocols, CRFs, original reports of test results, IMP dispensing logs, correspondence, records of informed consent, and other documents pertaining to the conduct of the study) must be retained. Documents should be stored in such a way that they can be accessed/data retrieved at a later date. Consideration should be given to security and environmental risks.

No study document will be destroyed without prior written agreement between the Sponsor and the investigator. Should the investigator wish to assign the study records to another party or move them to another location, written agreement must be obtained from the Sponsor.

#### Archiving

All trial documentation, including that held at participating sites and the trial coordinating centre, will be archived for a minimum of 10 years following the end of the study.

#### Data sharing

Individual de-identified participant data collected during the trial (including data dictionaries) will be available to share after publication. Data will be made available to researchers who provide a methodologically sound proposal, to achieve aims in the approved proposal. Proposals/requests should be directed to the Chief Investigator and requestors will be asked to sign a data access agreement. Data sharing requests will be shared with IDMC and TSC for their review and approval, respectively. In the event where no TSC or IDMC is available and the study is still active, the request is to be reviewed by the Head of Statistics, Director of Operations, and the Quality Assurance Manager.

### Confidentiality {27}

The investigator must ensure that the participant’s confidentiality is maintained. On the CRF or other documents submitted to the Sponsors, participants will be identified by a participant ID number only. Documents that are not submitted to the Sponsor (e.g., signed informed consent form) should be kept in a strictly confidential file by the investigator.

The investigator shall permit direct access to participants’ records and source documents for the purposes of monitoring, auditing, or inspection by the Sponsor, authorised representatives of the Sponsor, Regulatory Authorities, and RECs.

The investigators and study site staff will comply with the requirements of the Data Protection Act 2018 concerning the collection, storage, processing, and disclosure of personal information and will uphold the Act’s core principles.

It is the investigator’s responsibility to inform the participant’s routine doctor by letter that the participant is taking part in the study provided the participant agrees to this, and information to this effect is included in the Participant Information Sheet and Informed Consent. The participant’s GP will also be informed, providing participants agree to this. A copy of the letter should be filed in the Investigator Site File.

### Plans for collection, laboratory evaluation, and storage of biological specimens for genetic or molecular analysis in this trial/future use {33}

Samples will be collected according to the schedules in Tables 2 and 3 and analysed as described in Table 4. They will be stored in accordance with local laboratory practice, compliant to the Human Tissue Act 2004.

## Statistical methods

### Statistical methods for primary and secondary outcomes {20a}

Statistical methods for analysis of the study endpoints are described below. A separate detailed Statistical Analysis Plan (SAP) will be prepared and finalised prior to database lock. This will contain the rationale for the methods chosen and the assessment of their assumptions. It will include pre-specifying the handling of covariates and missing data and per protocol analyses. The per-protocol (PP) population will remove participants that are non-compliant in their treatment regimen. This will consist of the following: any participant that fails to successfully receive infusion (placebo or bNAb), any participant that fails to adhere to ATI, as established by detection of ART within blood sample, any participant that is lost-to-follow-up/withdrawn, any participant that fails to either (a) complete the 36-week follow-up period or (b) register viral rebound with the EAC. ITT population will include all participants randomised into the study according to their allocated arm at randomisation, regardless of treatment received. Changes to the plan will be re-approved by trial oversight committees.

Any deviations from the SAP will be documented and signed off by the statisticians and CI and filed in the statistics section of the Trial Master File (TMF) which will be merged with the main TMF at the end of the study.
Primary endpoint analysisAll the analyses will be on an intention-to-treat (ITT) principle and all statistical tests will be two-tailed with a 5% significance level. All participants screened eligible and enrolled in the trial will be included in the ITT analyses.The primary endpoint will be analysed using a time to event approach and differences will be tested using Cox proportional hazards models with censoring applied (as defined within the SAP). Kaplan-Meier curves detailing the survival function will also be presented.Secondary outcomes will be compared based on data type. Time to event outcomes will be assessed using the same Cox proportional hazards models described above. Paired data in Stage 2 will be assessed using a paired *t*-test (or alternate paired approach) and chi-squared / Fisher exact testing used for categorical variables. Further details to be provided in the SAP.Safety analysisSafety outcomes will be reported as unadjusted participant proportions and rates within and between arms with 95% confidence intervals using exact methods where appropriate.

An independent Endpoint Adjudication Committee will be set up to evaluate and review confirmed time of viral rebound in retrospect prior to the primary analysis. The committee will review all viral load data (blinded to study arm) and determine the date of confirmed viral load rebound. Any participant recommencing ART prior to viral rebound will also be reviewed by the committee as a potential endpoint. If established as not an endpoint, these participants will be censored at time of ART restart for analysis purposes.

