### Strategies to improve adherence to interventions {11c}

#### Adherence to ART

ART treatment compliance will be the responsibility of each study participant and their routine HIV physician. Investigators will promote compliance by providing instruction for participants to take ART exactly as prescribed during the course of the trial. Participant compliance to ART or remaining off ART will be closely monitored throughout the trial through regular HIV viral load monitoring. Blood measurement of ART levels will be undertaken retrospectively to ensure that for evaluation of the primary endpoint individuals with controlled viraemia are not on any ART drugs.

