### Sample size {14}

#### Sample size and power considerations

Stage 1—arm A compared to arm B

Underlying viral rebound rates at 36 weeks of 90% and 55% in the control and intervention groups respectively (i.e. 10% and 45% free from rebound by 36 weeks; hazard ratio 0.35) will be detected with 90% power using a two-sided log-rank test at the 5% significance level provided there are 31 participants per arm and no loss to follow-up or return to ART treatment prior to 36-week primary outcome. We propose to recruit 72 participants in order to provide an allowance of approximately 10% return to ART treatment, and loss to follow-up, prior to the earlier of either 36 weeks or a primary event.

Stage 2—arm B only

For patients in arm B, we will look at the within-person difference in ‘length of time undetectable (in days)’ between first and second period. Assuming a standard deviation of 14 days and a conservative correlation between the number of days in the first and second period of 0.7, 36 patients will allow detecting a difference of 6.6 days between the two periods with 90% power and two-sided alpha 0.05, including 15% dropout rate.

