### Methods for additional analyses (e.g. subgroup analyses) {20b}

Alongside the intention-to-treat analysis a per-protocol (PP) analysis will be carried out for some of the secondary outcome measures where participants that have withdrawn/lost-to-follow-up may potentially bias results. In addition to this, sensitivity analysis will be run on outcomes where protocol deviations may occur. These include investigations regarding missing data, and for the early restart of ART. Further details are provided within the SAP.

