### Methods in analysis to handle protocol non-adherence and any statistical methods to handle missing data {20c}

There is a possibility that a small proportion of participants will be affected by COVID-19, an intercurrent event, and will need to restart ART before reaching the primary endpoint. This might affect the power, diluting the treatment effect. Other participants may also elect to restart ART before concluding follow-up without experiencing a viral rebound event. We expect this proportion to be very small and to stay within the 10% assumption used within the power calculation, but it will be monitored by trial oversight committees and sample size will be adjusted if needed. For these cases, under most scenarios censoring at time of ART restart will naturally handle missing outcome data. However, based on the pattern and extent of missingness, if appropriate, we will explore the effect of alternative missing data assumptions within sensitivity analysis using a multiple imputation approach. Further details of which will be included within the Statistical Analysis Plan.

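### The per-protocol set is defined partly by whether follow-up or rebound was observed, so it can select on outcome instead of correcting for loss; its two follow-up limbs also conflict

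*Protocol article*

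**What the plan says.** Section {20a} (Statistical methods for primary and secondary outcomes) introduces the PP set as one of compliance: "The per-protocol (PP) population will remove participants that are non-compliant in their treatment regimen". It then lists four grounds for removal. Two concern treatment: the infusion was not received, or ART was detected in blood during the treatment interruption. The other two concern follow-up: "any participant that is lost-to-follow-up/withdrawn, any participant that fails to either (a) complete the 36-week follow-up period or (b) register viral rebound with the EAC".

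Section {20b} (Methods for additional analyses) states the purpose: "per-protocol (PP) analysis will be carried out for some of the secondary outcome measures where participants that have withdrawn/lost-to-follow-up may potentially bias results".

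The main analysis works differently. The same section {20a} puts it on an intention-to-treat (ITT) basis. When the Endpoint Adjudication Committee (EAC) decides that an early ART restart is not an endpoint, "these participants will be censored at time of ART restart for analysis purposes". Section {20c} expects censoring to deal with most missing outcomes and adds, if appropriate, that "we will explore the effect of alternative missing data assumptions within sensitivity analysis using a multiple imputation approach". Under Criteria for restarting ART, a participant may choose to restart at any time during the interruption, so doing so is not a breach of the allocated treatment.

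**The concern.** Two of the four exclusions are not about compliance, and one refers to the event itself. Take a participant who would leave at week 20. If rebound came at week 10, limb (b) keeps that person. If still suppressed at week 20, the person has neither 36 weeks nor a rebound and is deleted. Everyone deleted by the (a)/(b) rule is therefore without an adjudicated event when last seen. The slower-rebounding arm stays at risk longer, so it has more time to lose people in this way.

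This defeats the stated purpose. When dropout is unrelated to rebound, censoring uses the partial follow-up without bias, whereas deletion introduces a bias. When dropout is related to rebound, deletion does not remove that bias either. At stake is how any PP result placed beside the ITT result is read, since agreement or disagreement between them could come from the set definition.

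The limbs also do not fit together. The lost/withdrawn limb makes no exception for someone who has already rebounded, although follow-up continues after rebound. Read literally, it deletes a person whom limb (b) keeps. For early restarters it is unclear whether limb (a) means 36 weeks of attendance or 36 weeks off ART.

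**Working it through.** **Inputs from the protocol (Sample size and power considerations).** "Underlying viral rebound rates at 36 weeks of 90% and 55% in the control and intervention groups respectively", so 10% and 45% are rebound-free; 90% power, two-sided 5%, 31 per arm; 72 recruited to allow for about 10% early restart and loss.

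**The plan's own figure.** HR = ln(0.45)/ln(0.10) = 0.347. Freedman events = (1.960 + 1.282)² × [(1 + 0.347)/(1 − 0.347)]² = 10.51 × 4.25 = 44.7, so 45. The mean event probability is (0.90 + 0.55)/2 = 0.725, and 45/0.725 = 62.07, or 31.03 per arm. Power at 31 per arm is 90.2%. The stated 31 reproduces, so these design rates are a fair base for illustration. The protocol gives no rates for the secondary outcomes to which PP applies.

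**Reading 1: confirmed rebounders are kept.** Assume exponential rebound with weekly hazard λ = −ln(S36)/36, which is 0.0640 in arm B and 0.0222 in arm A. Assume dropout at constant weekly hazard c, independent of rebound. Then:
- rebound observed: E = λ/(λ + c) × [1 − exp(−36(λ + c))]
- 36 weeks completed without rebound: F = exp(−36(λ + c))
- deleted: 1 − E − F
- PP rebound-free proportion: F/(E + F)

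Worked case, c = 0.005:
- Arm A: E = 0.509, F = 0.376, deleted 0.115, rebound-free 0.376/0.885 = 0.425.
- Arm B: E = 0.850, F = 0.084, deleted 0.066, rebound-free 0.0835/0.9336 = 0.089.

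| Dropout (assumed) | Deleted A / B | Rebound-free A / B | HR implied by proportions |
|---|---|---|---|
| none | 0 / 0 | 45% / 10% | 0.347 |
| c = 0.005 (9.1% deleted overall) | 11.5% / 6.6% | 42.5% / 8.9% | 0.355 |
| 10% deleted overall (c = 0.00556) | 12.7% / 7.3% | 42.2% / 8.8% | 0.356 |
| c = 0.008 (13.9% overall) | 17.6% / 10.3% | 40.9% / 8.4% | 0.360 |
| 20% deleted overall | 25.1% / 14.9% | 38.8% / 7.6% | 0.367 |

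A Cox model on 20,000 simulated participants per arm agrees. At 10% overall, the HR is 0.346 with censoring and 0.359 in the PP set. At 20% it is 0.342 and 0.373.

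**Unequal loss (assumed).** With 2% of arm B and 18% of arm A deleted, the PP HR is 0.387. With the proportions reversed it is 0.296. The censored HR stays at 0.342 and 0.344.

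**Reading 2: everyone lost by week 36 is deleted, rebounded or not.** If loss is independent of rebound and runs at the same rate before and after it, deletion is 1 − exp(−36c) in both arms: 16.5% at 0.5% per week and 25.0% at 0.8% per week. The rebound-free proportions stay at 45% and 10%, and only precision is lost. This reading makes limb (b) ineffective for anyone who rebounds and is then lost.

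**The case against.** The strongest reply is that little depends on this. The primary analysis is ITT with censoring, and PP is run alongside it for some secondary outcomes only. At the planned level of loss the shift is 1 to 3 percentage points. The log HR moves by ln(0.356/0.347) ≈ 0.03, against a standard error of about √(1/32.4 + 1/19.8) = 0.29 with 36 per arm (32.4 and 19.8 expected events). The move is towards no effect. All of this stands and limits the weight of the point.

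It is also fair that the bias under random dropout depends on Reading 1. That stands too, but Reading 2 escapes the bias only by contradicting limb (b), and only if loss runs at the same rate before and after rebound.

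Three stronger inferences are tempting, and the documents do not support them:
- **That the trial's main result is biased.** No PP analysis of the primary endpoint is stated.
- **That the PP set will flatter the antibodies.** Deleting 15% of arm A's would-be rebounders as early restarters would raise its rebound-free proportion to 0.45/(0.45 + 0.55 × 0.85) = 49%. Nothing in the protocol supports 15%, and it is unclear whether restarters, who continue visits, fail limb (a) at all.
- **That ART testing is aimed only at suppressed participants.** The section Adherence to ART says "Blood measurement of ART levels will be undertaken retrospectively to ensure that for evaluation of the primary endpoint individuals with controlled viraemia" are not on ART drugs. That states a purpose. The Outcomes section already lists detectable ART by arm at weeks 12, 24, 36 and 48, without restriction by viral load.

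Nor is this simply a detail left to the analysis plan: the article states both the exclusion list and its rationale, and an analysis plan that follows it would inherit them.

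**Conclusion.** The point holds in a limited form. The PP definition mixes treatment adherence with completeness of follow-up, its two follow-up limbs conflict, and the reason given for it in {20b} is mistaken. If rebounders are kept, the set conditions on outcome. The size is small under equal random loss near 10% (rebound-free proportions about 42% and 9% in place of 45% and 10%, HR about 0.36 in place of 0.347), larger with more loss, and of either sign with unequal loss (0.30 to 0.39 in the cases tried). These figures assume exponential rebound at the design rates and dropout independent of rebound; every dropout pattern beyond the stated 10% allowance is an assumption. They borrow the primary endpoint's rates to show the mechanism and do not predict any particular secondary result. The primary analysis is not affected.

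**What to change.** - Define PP exclusions by treatment adherence alone: infusion received and treatment interruption started. Remove the lost/withdrawn limb and the (a)/(b) limb, which also resolves their conflict.
- For time-to-event outcomes, keep lost, withdrawn, early-restart and ART-positive participants and censor them at the last compliant visit. Section {20a} already censors at ART restart.
- For outcomes summarised as means or as percentages at fixed weeks, where censoring does not define an analysis, handle loss with the multiple imputation that section {20c} already foresees.
- In {20b}, delete the rationale that removing lost or withdrawn participants protects against bias.

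The cost is a wording change in the protocol and analysis plan, which section {20a} says is to be finalised before database lock, and slightly more analysis work. No new data are needed. Censoring at ART restart or at a positive ART sample still assumes that these events are uninformative given what is modelled, so the {20c} sensitivity analysis should accompany it.
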